## Abstract

**Background:**

The investigational medicinal product GKT137831 is a selective inhibitor of NOX 1 and 4 isoforms of the nicotinamide adenine dinucleotide phosphate (NADPH) oxidase family of enzymes, which has the potential to ameliorate diabetic kidney disease. An investigator-initiated, double-blind, randomised, placebo-controlled, multicentre phase 2 clinical trial started recruitment in December 2017, with the aim of evaluating the efficacy and safety of GKT13783, in adults with type 1 diabetes mellitus and persistently elevated urinary albumin excretion over a period of 48 weeks.

**Methods/design:**

The trial is currently recruiting in Australia and New Zealand, with recruitment expected to end on 30 June 2020. The primary outcome measure of the trial is the urinary albumin excretion level measured at 48 weeks of treatment. This statistical analysis plan presents an update to the published trial protocol and provides a comprehensive description of the statistical methods that will be used for the analysis of the data from this trial. In doing so, we follow the “Guidelines for the content of statistical analysis plans in clinical trials” to support transparency and reproducibility of the trial findings.

**Discussion:**

With the use of this prior statistical analysis plan, we aim to minimise bias in the reporting of the findings of this trial, which evaluates the investigational medicinal product GKT137831. The results of the trial are expected to be published in 2022.

**Trial registration:**

ANZCTR registry: ACTRN12617001187336. Registered on 14 July 2017.

Universal Trial Number: U1111-1187-2609; Protocol number: T1DGKT137831; Genkyotex trial number: GSN000241.

## Introduction

The kidney is a major target organ of microvascular damage in type 1 diabetes mellitus. Diabetic kidney disease affects 14–31% of people with type 1 diabetes mellitus [1], with studies showing that there is an urgent need for innovative treatment strategies to prevent, arrest, treat and reverse diabetic kidney disease [2].

The active investigational medicinal product evaluated in this study, a NOX1/4 inhibitor known as GKT137831 or setanaxib, has the potential to ameliorate diabetic kidney disease, and has been previously evaluated in people with type 2 diabetes mellitus and overt nephropathy (NCT02010242). The present trial is a separate study in people with albuminuria and type 1 diabetes mellitus [2] with a longer treatment duration and a higher dose. The overall objective of this trial is to evaluate the efficacy and safety of GKT137831 400 mg, taken twice a day, compared to placebo in adults with type 1 diabetes mellitus and elevated urinary albumin excretion.

Here, we provide a detailed description of the statistical methods that will be used for analysing the data obtained from this trial. In doing so, we followed the Guidelines for the content of statistical analysis plans in clinical trials [3], and care was taken to include the necessary information and sections as per these guidelines. This statistical analysis plan uses the recently published study protocol [2]. With the use of this statistical analysis plan, we aim to minimise reporting bias, supporting both transparency and reproducibility of the trial findings.

## Study methods

### Trial design

This is a multicentre, multi-national, phase 2, randomised, double-blind, placebo-controlled clinical trial with two parallel arms with 1:1 allocation ratio, which will test the effect of oral GKT137831 400 mg taken twice a day compared to placebo, on urine albumin to creatinine ratio, in adults with type 1 diabetes mellitus and persistent albuminuria despite optimal preceding standard of care treatment. The trial started recruitment in December 2017 and the recruitment is expected to end on 30 June 2020. The treatment period is 48 weeks with total study duration for the participant of up to 56 weeks. Figure 1 and Table 4 of the protocol [2] describe, respectively, the timeline for the study, which consists of 10 study visits in total, and the schedule of events.

### Randomisation

The randomisation ratio is 1:1 between the active drug (GKT137831) and placebo control arms, and is stratified by study centre and urinary albumin–creatinine ratio (UACR) level with the grouping defined as ≤ 35 mg/mmol or > 35 mg/mmol in female participants and ≤ 25 mg/mmol or > 25 mg/mmol in male participants using a minimisation strategy [4]. Participants will be randomised using a minimisation program integrated into the Interactive Web Response System, and is accessed live by sites through the website Randomize.net (see Sect. 3.3 of the protocol [2]).

### Sample size

Up to 284 participants in total are expected to be screened (anticipated screen fail rate up to 50%) with 142 participants each randomised to the treatment and placebo groups, to achieve 120 participants reaching the end of the treatment period in total (60 per treatment group). Sect. 2.5 of the protocol [2] provides details of the sample size calculations. In brief, the assumptions of the sample size calculations were the following: mean UACR of 13.56 mg/mmol in the control arm, difference between UACR means in the treatment arm of 3.56 mg/mmol/L (26% reduction in mean UACR in the treatment arm), equal standard deviations of 7.5 mg/mmol in the two arms, and within-subject correlation of 0.3. Using mixed model analysis of covariance with log-transformed UACR as the outcome, several scenarios were examined: 60 participants per treatment arm are required to achieve power > 90% with an alpha level of 0.05 and two-sided hypothesis testing, and 40 participants per treatment arm are required to achieve power > 90% with an alpha level of 0.05 and one-sided hypothesis testing.

### Trial framework

The primary analysis at the end of this trial will be a superiority comparison of GKT137831 versus placebo, where the null hypothesis to be tested for the primary and secondary endpoint analyses is that the effect of GKT137831 is no different to placebo and the alternative hypothesis is that GKT137831 is superior to placebo. The statistical hypotheses are described in detail in “Hypotheses” section. For the primary outcome, the minimal clinically important difference will be considered according to the sample size calculations in “Sample size” section; that is as a difference between UACR means in the treatment arms of 3.56 mg/mmol/L.

### Statistical interim analysis

There are no planned interim analyses.

### Timing of final analysis

All outcomes will be analysed collectively at the end of the trial at 48 weeks.

### Timing of outcome measures

The expected visit dates and visit windows are presented in Figure 1 of the protocol [2], and Table 4 of the protocol [2] describes the timing of all outcome measures.

## Statistical principles

### Confidence intervals and significance level

As the trial investigators have prior clinical knowledge about the directions of the effects on the endpoint UACR (primary outcome), midpoint UACR, endpoint and midpoint estimated glomerular filtration rate (eGFR) (secondary outcomes), the statistical tests for the primary and secondary hypotheses will be one-sided. For these outcomes, based on all the literature to date, there is no evidence to suggest that the placebo group will have a better outcome than the intervention group. The statistical tests for the safety and exploratory analyses will be two-sided. All the statistical tests will be performed using a 5% significance level, and we will report the 95% confidence interval. No adjustment for multiplicity is needed for the primary hypothesis. Testing for multiple comparisons in the secondary and exploratory hypotheses will be accounted for by adjusting the *p* values obtained from these analyses using the Benjamini-Hochberg method [5].

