### Hypotheses

#### Primary hypothesis

The null hypothesis is that the population mean of the endpoint UACR in the intervention group is the same as that in the placebo group (after adjustment for baseline UACR). The alternative hypothesis is that the population mean of the endpoint UACR is lower in the intervention group, compared to that in the placebo group (after adjustment for baseline UACR*)*.

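### One-sided 5% tests are reported with a 95% confidence interval, so a result can be called superior while its interval includes no effect; the 60 per arm matches the plan's two-sided scenario

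*SAP article*

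**What the plan says.** In the SAP section on confidence intervals and significance level, "the statistical tests for the primary and secondary hypotheses will be one-sided", on the ground of prior clinical knowledge about the direction of effect. The next rule covers every test: "All the statistical tests will be performed using a 5% significance level, and we will report the 95% confidence interval". In the same paragraph, "The statistical tests for the safety and exploratory analyses will be two-sided", so one interval level serves both kinds of test. Nothing says that the interval is a one-sided bound for some outcomes and two-sided for others. Table 3 puts a 95% confidence interval next to the p value for all four primary and secondary outcomes in three analysis sets, and the Fig. 2 caption uses 95% intervals again.

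The directional choice is carried through to the hypotheses. For the primary outcome, "The alternative hypothesis is that the population mean of the endpoint UACR is lower in the intervention group". For eGFR the alternatives are that it is higher on the drug.

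The Sample size section gives two scenarios. In one, "60 participants per treatment arm are required to achieve power > 90% with an alpha level of 0.05 and two-sided hypothesis testing". In the other, "40 participants per treatment arm are required to achieve power > 90% with an alpha level of 0.05 and one-sided hypothesis testing". The target adopted is 120 participants completing treatment, 60 per arm.

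**The concern.** The test and the interval use different thresholds for the same claim. When they disagree, the main results table would show a significant p value beside an interval that crosses no effect, with no rule for what the trial then concludes. If the choice is left until the data are seen, it could decide the headline.

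The sizing adds to this. The trial is recruited to the number that the plan attaches to a two-sided 5% test but is analysed with a one-sided 5% test, which allows twice the false-positive rate for benefit. For eGFR, the directional alternative also leaves no formal test for a decline on the drug.

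**Working it through.** **1. Thresholds.** A one-sided 5% test rejects when z > 1.645. A two-sided 95% interval excludes no effect only when |z| > 1.960. They disagree for z between 1.645 and 1.960, which is one-sided p from 0.025 to 0.05.

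**2. Inputs from the Sample size section.** Control mean 13.56; difference 3.56, so treatment mean 10.00; SD 7.5 in each arm; within-subject correlation 0.3; log-transformed outcome; analysis of covariance. The full calculation is in the protocol, which is not at hand. The conversion to the log scale by lognormal moment-matching is therefore an assumption.

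- Log variance = ln(1 + SD²/mean²). Control: ln(1 + 0.3059) = 0.2669, log SD 0.517. Treatment: ln(1 + 0.5625) = 0.4463, log SD 0.668. Pooled log SD = √((0.2669 + 0.4463)/2) = 0.597.
- Log mean = ln(mean) − variance/2. Control: 2.6071 − 0.1335 = 2.4737. Treatment: 2.3026 − 0.2231 = 2.0794. Difference 0.394.
- SE at 60 per arm with baseline adjustment = 0.597 × √(1 − 0.3²) × √(2/60) = 0.104.
- Expected z = 0.394/0.104 = 3.79 (3.62 without adjustment).

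**3. Reproducing the plan's figures.** Power = Φ(expected z − critical z), ignoring the opposite tail. In each row the lower figure is unadjusted and the higher one is adjusted for baseline.

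| Per arm | Test | Power |
|---|---|---|
| 60 | two-sided 5% | 95.1% to 96.6% |
| 40 | one-sided 5% | 90.4% to 92.6% |
| 40 | two-sided 5% | 84.0% to 87.2% |
| 60 | one-sided 5% | 97.6% to 98.4% |

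Both stated scenarios exceed 90%, as the plan says. Forty per arm does not reach 90% two-sided.

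**4. Chance of disagreement** = Φ(1.960 − expected z) − Φ(1.645 − expected z).

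- No effect (expected z = 0): 0.975 − 0.950 = 2.5%.
- Full design effect, 60 per arm: 1.8% adjusted, 2.5% unadjusted.
- Half the design effect (expected z = 3.79/2 = 1.90): Φ(0.06) − Φ(−0.25), about 12%. This is close to the maximum, which lies midway between the two thresholds.

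This chance equals the difference between one-sided and two-sided power at the same effect, here 98.4% − 96.6% = 1.8 points. The size of the problem and the power cost of the two-sided fix are thus one quantity, and must be quoted at the same assumed effect.

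**5. Example.** At 60 per arm with SE 0.104 and z = 1.8, the ratio is exp(−1.8 × 0.104) = 0.829 and one-sided p = 0.036. The 95% interval is exp(−0.187 ± 1.96 × 0.104) = 0.676 to 1.017. The 90% interval, using 1.645, is 0.699 to 0.984. The test declares superiority, the 95% interval includes 1, and the 90% interval agrees with the test.

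**6. Sensitivity to the reconstruction.** A raw-scale analysis of covariance with the same inputs gives 86.0% one-sided and 77.8% two-sided at 60 per arm, a gap of 8.2 points. That reading does not reproduce the plan's claim of more than 90%, and the plan specifies the log scale, but it shows how far the cost could move.

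**The case against.** One-sided testing is prespecified, disclosed, given a reason and consistent with the directional hypotheses, and a one-sided 5% scenario appears among the sample size calculations. In a phase 2 trial meant to inform phase 3, accepting a 5% chance of a false positive for benefit is a judgement that others may share. Having more participants than a one-sided test needs is not an error. All of this stands. A reader might infer that one-sided testing is itself the defect; the document does not support that. The defect is the unreconciled pairing with the 95% interval and with the two-sided sizing.

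A reader might also infer that harm on eGFR could not be shown. That goes too far. Table 3 reports the estimated difference and a 95% interval for endpoint and midpoint eGFR, and a two-sided interval lying wholly below zero would show a decline. What is missing is a formal test in that direction.

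The 95% interval could be meant as a one-sided bound, which would agree with the test. The plan never says so, and it uses the same unqualified interval for tests it calls two-sided.

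Finally, both the p value and the interval will be printed, so a reader can apply the stricter criterion. This limits the damage but does not supply the missing decision rule.

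**Conclusion.** The mismatch holds. As written, the test and the interval for the primary and secondary outcomes apply different standards, and nothing says which one governs. The chance of visible disagreement is 2.5% under no effect, about 2% at the full design effect with 60 per arm, and up to about 12% near half that effect. The last two figures rest on the lognormal reconstruction and a normal approximation. It would be wrong to apply the 12% to the design effect itself.

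The false-positive rate for benefit is 5%, against 2.5% under the two-sided scenario that matches the adopted 60 per arm. That comparison needs no reconstruction.

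For the secondary outcomes the plan also adjusts p values by the Benjamini-Hochberg method, so the exact range of disagreement above applies to their unadjusted p values.

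This should be fixed. It does not make the results uninterpretable.

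**What to change.** Preferred: state that the primary and secondary hypotheses are tested two-sided at 5%, and keep the two-sided 95% interval. Reword the alternatives in the Trial framework and Hypotheses sections to match. A one-sided 2.5% test is equivalent for a claim of benefit and also agrees with the interval, but only the two-sided form adds a formal test for an eGFR decline.

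The change needs no more participants, because the plan itself states more than 90% power for this test at 60 per arm. The cost is some power: about 2 points (98.4% to 96.6%) under the log-scale reconstruction with baseline adjustment, and about 8 points (86.0% to 77.8%) under the raw-scale reading.

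If one-sided 5% is retained, report a two-sided 90% interval for these outcomes in Table 3 and Fig. 2, or a one-sided 95% bound labelled as such. This costs no power but leaves the false-positive rate for benefit at 5%, and a one-sided bound alone could hide an eGFR decline. Either way, settle the wording before unblinding.

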### Adherence and protocol deviations

#### Definition of adherence

Study drug treatment adherence for each visit interval is defined as taking at least 80% of the required study drug dosage. For each participant, this will be based on the percentage compliance calculated as: percent compliance = (number of capsules taken by the participant/number of capsules the participant should have taken) *100%. In this study, the participants will be taking four capsules twice a day.

#### Presentation of adherence

The number and percentage of participants taking more than 80% of the required study drug will be presented by treatment arm and visit (see Table 1), and the descriptive statistics on the percentage compliance will also be presented. No formal statistical testing will be performed.

**Table 1 Tab1:** The number and percentage of participants taking more than 80% of the prescribed treatment

Visit number^a^	Treatment group	
	GKT137831 N (%)	Placebo, *N* (%)
4		
5		
6		
7		
8		
9		
10		

^a^ Visit number refers to Figure 1 of the protocol [1]

#### Definition of protocol deviations

Protocol deviations, “any change, divergence, or departure from the study design or procedures in the protocol [2]”, are defined according to the International Conference on Harmonisation of Technical Requirements for Registration of Pharmaceuticals for Human Use (ICH) guideline E3 on Structure and Content of Clinical Study Reports July1996 [6], classified as either “important” or “non-important”. Important protocol deviations are deviations that may significantly impact the completeness, accuracy, and/or reliability of the study data or that may significantly affect a subject’s rights, safety, or well-being. Non-adherence as defined in “Definition of adherence” section will be considered an important protocol deviation. Deviations that do not fit this definition are non-important.

#### Presentation of protocol deviations

Protocol deviations will be summarised by treatment arm, using the number and percentage of participants with important and non-important protocol deviations, and details on the type of deviation. The percentages will be calculated based on the participants in the intention-to-treat (ITT) analysis set as the denominator. No formal statistical testing will be performed. The details of protocol deviations including adherence will be added as an aide memoire to Fig. 1.

**Fig. 1 Fig1:**
[figure not shown]
A flow diagram of the trial based on Consolidated standards of reporting trials (CONSORT) 2010

### Analysis populations

The following four analysis sets will be used in the study.

#### Main analysis set (ITT analysis set)

The ITT analysis set is the main analysis set that will be used for evaluating the primary hypothesis, and it consists of all randomised participants with each participant retaining their treatment group as originally allocated by the randomisation procedure.

#### Modified intention-to-treat analysis set

The modified ITT analysis set consists of participants who have been randomised and have taken at least one capsule of investigational product or placebo, with each participant in the set retaining their treatment group as originally allocated by the randomisation procedure.

### Safety analysis set

The safety analysis set consists of all participants who have taken at least one capsule of investigational product or placebo and have at least one subsequent safety assessment, which is described in Sect. 4.2 of the protocol [2].

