### Withdrawals/follow up

The number of participants at each level of withdrawal will be documented and the timing of withdrawals will be presented in the CONSORT diagram in Fig. 1, categorized as (1) withdrawn from the intervention but continued with follow up, (2) withdrawn from follow up but allowed data collected to date to be used, (3) withdrawn from follow up and withdrawn consent for data collected to date to be used, and (4) lost to contact/follow up.

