#### Safety outcome measures

The key safety outcome measures are treatment-emergent adverse events and abnormal laboratory analytes as defined in the protocol [1] Sect. 10.4.4.2 and 10.4.4.3, respectively. All safety outcome measures are given in Supplementary Table 2 along with references to the sections where they are defined in the protocol [1].

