##### Additional analyses

Supplementary analyses will be completed by repeating the main analysis described in “Main analysis model” section - “Sensitivity analyses” section using (1) the modified ITT and (2) the PP analysis sets, and these results will be reported in the proposed format.

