#### Safety analyses

Safety analyses will be based on the safety analysis set described in “Safety analysis set” section. The safety outcomes presented in Supplementary Table 2 will be summarised by group (intervention and placebo). Categorical variables will be summarised using frequencies and percentages, and the continuous variables will be summarised using appropriate central tendency and dispersion measures, and presented either as mean and standard deviation (SD) or median and 25th–75th percentile. Percentage standardized differences between the two groups will be calculated for all variables. A value ≥ 10% difference will be taken as a meaningful difference between the groups. In addition, where possible, a linear mixed model or a generalised linear mixed model will be used with the safety measure at the end of the trial as the outcome, a categorical variable indicating the group structure (intervention or placebo group) as the exposure, and the safety measure at the beginning of the trial as a covariate, also accounting for centre variability. Where appropriate, an estimate of the group effect, 95% confidence interval and *p* value will be presented. The results will be summarised in Table 5.

**Table 5 Tab5:** Safety analyses results using the safety analysis set

Safety outcome measure	Values		Percentage standardized difference	Estimated difference^a^	95% Confidence Interval^a^	*P* value^a^
	Intervention (GKT137831) group (*n* = xxx)	Placebo group (*n* = xxx)				
Treatment-emergent adverse events, *n* (%)						
Abnormal laboratory analytes, *n* (%)						
Abnormal physical examination and vital signs, *n* (%)						
QT corrected electrocardiogram (ECG), mean (SD)						
Treatment-emergent qualitative ECG, *n* (%)						
Concomitant medications, *n* (%)						
Systolic blood pressure (mmHg), mean (SD)						
Diastolic blood pressure (mmHg), mean (SD)						
Heart rate (beats per minute), mean (SD)						
Weight (Kg), mean (SD)						

*SD* standard deviation

^a^ If feasible to carry out testing; in the intervention group compared to the placebo group

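### The safety set requires a safety assessment after dosing, so a dosed participant whose early event ends participation can drop out of Table 5, unless the protocol counts an adverse event report as an assessment

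*SAP article*

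**What the plan says.** Under Analysis populations, the Safety analysis set consists of participants who "have taken at least one capsule of investigational product or placebo and have at least one subsequent safety assessment". For the meaning of a safety assessment the SAP refers to Sect. 4.2 of the protocol.

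The Safety analyses section states: "Safety analyses will be based on the safety analysis set described in" the section of that name. No other set is named for safety. The same section says "Categorical variables will be summarised using frequencies and percentages", by group, and sends the results to Table 5. Under Safety outcome measures, "The key safety outcome measures are treatment-emergent adverse events and abnormal laboratory analytes".

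The SAP also defines a set by exposure without the second condition. The Modified intention-to-treat analysis set consists of "participants who have been randomised and have taken at least one capsule of investigational product or placebo". Under Additional analyses, that set serves supplementary repeats of the efficacy analysis.

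The Withdrawals/follow up section provides for participants who withdraw from follow-up and for those "4) lost to contact/follow up".

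**The concern.** The second condition is met or failed after dosing. A reaction soon after the first capsules, or a death or withdrawal because of one, is among the things that can prevent a later assessment. Membership of the safety set may then depend on the outcome that the set is meant to measure.

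A participant outside the set contributes neither an event nor a person at risk to Table 5. If such events are known to the trial, are not treated as assessments and arise more often on GKT137831, the table understates the active-arm rate by more than the placebo rate. Nothing in the SAP retains these participants, lists them separately or says that a reported event satisfies the condition.

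**Working it through.** The SAP states no figure on this point, so there is nothing to reproduce. The check compares the definitions and then illustrates the scale.

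**Definitions side by side**

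| Set | One capsule or more | Later safety assessment | Used for |
|---|---|---|---|
| Modified ITT | required | not required | supplementary efficacy repeats |
| Safety | required | required | all safety analyses, Table 5 |

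A dosed participant with no later assessment is in the first set and not in the second. Because categorical safety outcomes are reported as counts and percentages of the safety set, that participant leaves both parts of the fraction.

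**Inputs for the illustration**

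- *n*, dosed per arm. The Sample size section gives up to 284 screened and up to 50% screen failure: 284 × 0.5 = 142 randomised in total, or 142 / 2 = 71 per arm. The sentence can also be read literally as 142 per arm, so both values are shown. That everyone randomised is dosed is an assumption.
- *e*, participants in the arm with an event: 3, 7 or 14 (assumed).
- *k*, those among the *e* who have no later assessment although their event is known: 0 or 1 here (assumed).

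**Formula**

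Rate among all dosed: e/n. Rate under the SAP's definition: (e − k)/(n − k).

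For k = 1 the difference is e/n − (e − 1)/(n − 1) = (n − e)/[n(n − 1)].

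| n | e | e/n | (e − 1)/(n − 1) | Loss for k = 1, points |
|---|---|---|---|---|
| 71 | 3 | 4.2% | 2.9% | 68/4970 = 1.4 |
| 71 | 7 | 9.9% | 8.6% | 64/4970 = 1.3 |
| 71 | 14 | 19.7% | 18.6% | 57/4970 = 1.1 |
| 142 | 3 | 2.1% | 1.4% | 139/20022 = 0.7 |
| 142 | 7 | 4.9% | 4.3% | 135/20022 = 0.7 |
| 142 | 14 | 9.9% | 9.2% | 128/20022 = 0.6 |

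For k = 0 the two rates are equal and the loss is zero.

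**The opposite case**

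A dosed participant lost with no known event adds nothing to the numerator under either definition. Leaving that person out raises the rate slightly: with n = 71 and e = 7, 7/70 = 10.0% against 7/71 = 9.9%. So the direction depends on who is excluded.

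**The case against.** The strongest reply is that the SAP hands the meaning of a safety assessment to a section that is not shown. The SAP says only that the assessment is described there, not that it must be a scheduled visit. If an adverse event report counts, a participant whose early event is reported stays in the set and no known event is lost. This stands, and it makes the point conditional. It does not remove it: the SAP never says that a report counts, and even if it did, a dosed participant without a report would still be excluded because of what happened after dosing.

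Second, early exits remain visible. The Recruitment and Withdrawals/follow up sections put withdrawals and losses into the CONSORT diagram, including reasons and timing. This is true and useful, but it does not restore anyone to Table 5.

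Third, the modified ITT and safety sets serve different purposes and may differ. That is fair. The contrast is not a contradiction; it shows only that an exposure-only definition is already in the SAP.

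A reader might also infer more than the document supports:

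- *That the rule favours the drug.* The SAP does not establish this. Exclusions without a known event work the other way, as shown above.
- *That the understatement is large.* Assuming 5 events, 2 of them unassessed, gives 3/69 = 4.3% instead of 5/71 = 7.0%, about 38% lower in relative terms. Both counts are invented, and the document supports neither.
- *That the absence of a rule for participants who took the other arm's capsules is a defect.* A condensed article can leave that detail to the full plan, and it is not part of this point.

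**Conclusion.** The point holds in a conditional form. As written, the safety set can exclude a dosed participant whose early event ends participation before any assessment, and that participant is then missing from both parts of the Table 5 percentages. Whether known events are actually lost depends on whether Sect. 4.2 of the protocol treats an adverse event report as an assessment.

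The number affected is probably small and cannot be derived from the SAP. Per dropped participant with a known event, the arm's rate falls by about 1.1 to 1.4 percentage points at an assumed 71 dosed per arm, or 0.6 to 0.7 points at 142, over assumed event counts of 3 to 14. It falls by nothing if no one is dropped. A bias in favour of the drug arises only if such events are known, do not qualify as an assessment and occur more often in the active arm.

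The change is worth making because it removes a selection after dosing from the safety tables at almost no cost.

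**What to change.** In the Safety analysis set section, define the set as all participants who took at least one capsule and delete the condition on a later assessment. State that every adverse event reported from the first capsule onwards is counted. In Table 5, show participants with no post-baseline laboratory, ECG or vital-sign value as missing in those rows only.

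The cost is one or two sentences in the SAP and no new data. The downside is that a few participants will contribute only to the adverse event rows, and those with no reported event will enter the denominator only, which lowers the reported rate slightly.
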